### Methods for additional analyses (e.g., subgroup analyses) {20b}

The primary endpoint analysis will be supplemented by three exploratory subgroup analyses based on age (< 65 years, ≥ 65 years), MCI subtype based on the baseline cognitive assessment values (amnestic MCI, non-amnestic and multi-domain MCI), and gender (male, female). The results of all subgroup analyses will be presented in a combined table and a forest plot, including effect size estimators (η^2^) and a 95% confidence interval (CI). The table will also include the number of patients in each respective subgroup and the *p* values. The explorative statistical analysis of secondary outcomes in the post-COVID group (see {12}) follows, where appropriate, the outlined approach for the primary endpoint, see {20a}.

Furthermore, the S-NAB scores and CFQ-D values at baseline and follow-up will be standardized using *z*-scores to determine cognitive performance estimation accuracy. The average discrepancy scores between groups will be analyzed using *t*-tests and correlational analysis.

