## Introduction

### Background and rationale {6a}

Mild cognitive impairment (MCI) is characterized by a noticeable decrease in at least one cognitive domain, surpassing what is typically expected for an individual’s age level. However, MCI does not significantly hinder a person’s ability to carry out their daily activities and the general functional independence is maintained. The impacted cognitive domains can include memory, attention, executive function, language, and visuospatial processing [1, 2]. Based on the affected cognitive abilities, MCI can be further classified as single-domain or multi-domain MCI, as well as amnestic or non-amnestic MCI [2, 3]. Single-domain MCI refers to cases where only one cognitive domain is affected, while multi-domain MCI involves the impairment of multiple cognitive domains. Amnestic MCI is the most common subtype and relates to memory impairment as the predominant feature. On the other hand, non-amnestic MCI involves impairments in cognitive domains other than memory, such as attention, executive function, or language [2]. In the International Classification of Diseases—German Modification (ICD-10-GM; [4]), MCI is classified as mild cognitive disorder under the code F06.7.

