## Objectives {7}

The multicenter randomized controlled study aims to investigate the effectiveness of the NeuroNation MED training app on the cognitive abilities of patients with MCI. The intervention group (IG) will utilize the app for a duration of 12 weeks, with a recommended training intensity of three sessions per week, each lasting approximately 25 to 40 min. The wait list control group (CG) can receive their regular conventional medical care prescribed by a physician or no medical care at all, but will not have access to the training app or use any other cCT during the study period.

The primary objective of this study is to determine the effectiveness of the training program in improving the cognitive abilities of individuals with MCI. Additionally, the study aims to investigate the influence of the training program on subjective cognitive functioning, health competence, depressive and anxious symptoms, and psychological well-being. Also, the usability of the provided training program will be evaluated. Furthermore, patient diaries will be utilized to gather comprehensive information regarding additional cognition-oriented lifestyle activities and therapies that are not part of the intervention.

Primary research question:Does a 12-week mobile self-administered cCT program improve cognitive abilities of patients with MCI?H0: There is no significant difference in the index score of the screening module of the Neuropsychological Assessment Battery (S-NAB) between IG and CG.H1: There is a significant difference in the index score of the S-NAB between the IG and CG, favoring the IG.

Secondary research questions:Does the use of the mobile cCT program lead to an improvement in depressive and anxious symptoms, subjective cognitive functioning, psychological well-being, and health-related competence in patients with MCI?Are there associations between the usage of the NeuroNation MED app, sociodemographic data, and changes in cognitive and psychosocial outcomes within the intervention group?How do participants within the IG perceive and evaluate the usability of the NeuroNation MED app?

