To achieve comparability between the experimental groups at baseline, the IG and CG will be compared in terms of sociodemographic characteristics. The independent samples Welch’s *t*-test will be used for normally distributed metric variables, while the chi-square test will be employed for categorical variables. If a normal distribution is not found in the data collected, the Wilcoxon signed-rank test or Mann–Whitney *U* test will be applied. ANCOVA will be conducted to evaluate the training effects between the IG and CG, using the baseline values as a covariate and incorporating gender, experimental group (IG and CG) as independent variables, and the post-assessment score as dependent variable. Additionally, age and study center will also be examined as covariates. If the data fail to meet the assumptions for performing parametric ANCOVA, non-parametric tests such as the Wilcoxon test or Mann–Whitney *U* test will be applied instead. Effect sizes and confidence intervals will be calculated for the respective statistical tests to enhance result interpretability.

Using the logging data from the NeuroNation MED app, Pearson correlations will be used to examine the relationships between the number of training days, completed training units, and changes in assessments within the IG. Furthermore, one-way ANOVA will be employed to investigate potential associations between usage frequencies and sociodemographic data.

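### The only effect measure named for the exploratory subgroup forest plot is eta-squared, which has no sign, so benefit and harm would plot at the same point

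*Protocol article*

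**What the plan says.** Section {20b} of the protocol article states that the primary endpoint analysis will be "supplemented by three exploratory subgroup analyses based on age", MCI subtype and gender. The results will be "presented in a combined table and a forest plot, including effect size estimators (η^2^) and a 95% confidence interval (CI"). It adds: "The table will also include the number of patients in each respective subgroup and the *p* values". No signed measure, such as a mean difference or Cohen's d, is named there. Nor does the text say whether the p values belong to each subgroup or to a comparison between subgroups.

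The subtype factor is given as "MCI subtype based on the baseline cognitive assessment values (amnestic MCI, non-amnestic and multi-domain MCI"). The background section {6a} describes two separate axes: "MCI can be further classified as single-domain or multi-domain MCI, as well as amnestic or non-amnestic MCI".

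Two other places bear on the point. The alternative hypothesis in section {7} has a direction: "There is a significant difference in the index score of the S-NAB between the IG and CG, favoring the IG". The main model in section {20a} is an ANCOVA: "ANCOVA will be conducted to evaluate the training effects between the IG and CG, using the baseline values as a covariate". That section also promises effect sizes and confidence intervals in general, without naming a measure.

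**The concern.** A subgroup forest plot exists to show, for each subgroup, which way the effect points, how large it is and how precisely it is known. Eta-squared does not give direction, and its size is not in units a clinician can interpret. Because it is bounded at 0, the plot has no null line with benefit on one side and harm on the other. A subgroup that did worse with the app would sit where an equally strong benefit would sit. Eta-squared also lies above 0 on average when there is no effect, and more so in smaller subgroups, so subgroups of unequal size are not compared on an even footing.

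Two smaller matters affect the same table. Readers cannot tell what the p values test. The subtype labels also mix the two axes of section {6a}, so it is unclear into which row some patients fall.

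**Working it through.** **Inputs.** From section {14}: 164 IG and 82 CG (2:1, total 246), effect size 0.39, two-sided 0.05, power 80%. From section {12}: S-NAB mean 100, SD 15. The documents give no subgroup sizes. Where a subgroup is needed, I assume an equal split into halves of 82 IG and 41 CG (N = 123). The baseline adjustment is left out because no baseline to follow-up correlation is given.

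**The plan's own figure.** A noncentral t calculation with sample size scaled by the Wilcoxon-Mann-Whitney efficiency 3/π gives 82 CG and 246 in total, with power 0.801. The stated sample size is reproduced. The plan states no figure for subgroups.

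**Step 1: the sign is lost.** For two groups, F = d² × n1 × n0 / (n1 + n0) and eta-squared = F / (F + N - 2).
- Full sample: F = 0.1521 × 164 × 82 / 246 = 8.31, and eta-squared = 8.31 / (8.31 + 244) = 0.033.
- Because d enters only as d², +0.39 and -0.39 give the same F, the same p and the same interval. Intervals for eta-squared come from inverting the noncentral F; those for d use d ± 1.96 × √(1/n1 + 1/n0).

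| Sample | d | p | eta-squared (95% CI) | signed 95% CI for d |
|---|---|---|---|---|
| 164 / 82 | +0.39 | 0.0043 | 0.033 (0.003 to 0.088) | 0.12 to 0.66 |
| 164 / 82 | -0.39 | 0.0043 | 0.033 (0.003 to 0.088) | -0.66 to -0.12 |
| 82 / 41 (assumed) | +0.39 | 0.044 | 0.033 (0.000 to 0.116) | 0.02 to 0.76 |
| 82 / 41 (assumed) | -0.39 | 0.044 | 0.033 (0.000 to 0.116) | -0.76 to -0.02 |

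On the signed scale the two cases separate completely. If the trial SD equals the normative 15 (an assumption), they are 0.39 × 15 = 5.85 index points in opposite directions. The half-size rows show a further awkwardness: the 95% interval for eta-squared reaches 0 although p is below 0.05, whereas the signed interval agrees with the p value.

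**Step 2: the null value depends on subgroup size.** With no effect, the expected eta-squared in a two-group comparison is 1/(N - 1).
- N = 246: 1/245 = 0.004.
- N = 123: 1/122 = 0.008.

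This is small beside 0.033, but it always pushes upward and doubles when the sample is halved.

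**Step 3: why the p values should be named.** Suppose the true effect is 0.39 in both halves.
- Power within one half is 0.525. If the p values were within-subgroup, exactly one half would be significant with probability 2 × 0.525 × 0.475 = 0.50, although the effects do not differ.
- For an interaction, the standard error is √(2 × (1/82 + 1/41)) = 0.27. Power to detect a difference of 0.39 between the halves is about 0.30.

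The two kinds of p value answer different questions, so the table must say which it reports.

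**Step 4: the subtype labels.** Set beside section {6a}, the list in section {20b} can be read in three ways.
- As three literal levels, an amnestic multi-domain or non-amnestic multi-domain patient fits two of them.
- As two levels (amnestic against non-amnestic and multi-domain), an amnestic multi-domain patient fits both.
- As shorthand for single-domain amnestic, single-domain non-amnestic and multi-domain, the levels are disjoint.

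**The case against.** The strongest reply is that the wording does not limit the display to eta-squared. It says the display will include it, so a signed estimate could be added. Section {20a} also plans means, standard deviations and confidence intervals for both groups at baseline and 12 weeks. This stands to the extent that one cannot say harm in a subgroup would go unseen. It does not close the gap, because section {20a} does not promise those summaries by subgroup, and the one measure that section {20b} does fix is unsuitable for the plot.

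On the upward bias, the table will show each subgroup's size and interval, and signed estimates also scatter more in small subgroups. That is fair, and this is a minor part of the point. The difference is that signed estimates scatter around zero when there is no effect, while eta-squared lies above it.

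A reader might infer that the p values are within-subgroup and that the plan would therefore generate false claims of differential effect. The documents do not support this. The text does not specify the p values, an interaction test may stand in an analysis plan that is not shown, and no claim of effect modification is planned. A reader might also infer that the MCI subtypes definitely overlap. The disjoint reading is available, and the subtypes are to be derived from baseline test values, so a rule assigning each patient to one level may exist elsewhere. This is an ambiguity and not a proven error.

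**Conclusion.** The point holds for what section {20b} states: the only effect measure named for the subgroup table and forest plot is unsigned and bounded at 0, which suits a directional hypothesis poorly. At the design's own figures, +0.39 and -0.39 are indistinguishable (both about 0.033, 95% CI 0.003 to 0.088). That identity is algebraic and needs no assumption about subgroup size. The half-size results, the discordance probability of 0.50 and the interaction power of 0.30 rest on an assumed equal split and ignore covariate adjustment. The p values and the subtype labels need clarification only. The subgroup analyses are labelled exploratory, so the primary conclusion is unaffected and the importance is modest.

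**What to change.** - **Effect measure.** In the table and forest plot, show the adjusted IG minus CG difference in S-NAB index points with its 95% CI for each subgroup, from the planned ANCOVA extended by the subgroup factor and its interaction with group. Draw the null line at 0 and label the side that favours the app. Eta-squared can stay as an extra table column if wanted.
- **P values.** State that the reported p value is the one for the group-by-subgroup interaction, one per factor. Note that power for it is low, so a non-significant result does not show equal effects.
- **Subtypes.** State mutually exclusive levels and the rule that assigns patients from the baseline scores. Either define the three levels as single-domain amnestic, single-domain non-amnestic and multi-domain, or treat amnestic/non-amnestic and single-/multi-domain as two separate factors.

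The cost is a few lines of wording and a revised table shell, with no new data or assessments. It is best done before any subgroup results are produced.

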### Sample size {14}

The assumed effect size is based on results of previous studies using the cognitive training program “NeuroNation BT” [69] and comparable digital cognitive training applications [25, 26, 36, 70]. A calculation by means of a *t*-test for independent samples was used as the basis for the sample size calculation within the trial described here. With an allocation ratio of 2:1, if 164 subjects are included in the IG and 82 subjects are included in the control group, differences with an effect size of 0.39 or greater can be shown (a priori power analysis, Wilcoxon-Mann–Whitney test (two groups), power = 80%, two tails significance level *α* = 0.05). This resulted in the total sample size of 246. We expect a drop-out rate of approximately 15% [71], which results in a sample size to be recruited of *N* = 286. This sample size calculation was performed with G*Power 3.1.

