### Methods in analysis to handle protocol non-adherence and any statistical methods to handle missing data {20c}

Excluding participants with missing values from the analysis can bias the statistical analysis. Hence, a multiple imputation approach is conducted. Missing value information will be gathered through follow-up telephone interviews when a participant withdraws from the study. These interviews will assess the reasons for discontinuation.

Within this study, all of the missing data will be imputed. This process will involve the generation and pooling of multiple complete datasets, where missing values are estimated based on the observed data. To assess the robustness of our imputations and the potential impact of missing data on the study’s primary outcome, sensitivity analysis will be conducted using delta adjustment. Moreover, an intention-to-treat analysis will ensure that every participant who took part in the baseline assessment is included in the final analysis. This includes the IG, regardless of their adherence to the proposed training protocol.

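### The S-NAB/CFQ-D discrepancy is compared between arms by t-test at an unstated time point; the plan's own baseline-adjusted ANCOVA would be more precise at almost no cost

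*Protocol article*

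**What the plan says.** The protocol article, Methods for additional analyses {20b}, sets out an analysis of how accurately participants judge their own cognition. In it, "the S-NAB scores and CFQ-D values at baseline and follow-up will be standardized using *z*-scores", and then "The average discrepancy scores between groups will be analyzed using *t*-tests and correlational analysis". No time point, change score or covariate is named, and the article does not say whether the discrepancy is signed or absolute.

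For training effects, Statistical methods {20a} takes a different route: "ANCOVA will be conducted to evaluate the training effects between the IG and CG, using the baseline values as a covariate". The dependent variable there is the post-assessment score, gender enters alongside the experimental group, and age and study centre are also to be examined. Implementation {16c} stratifies the randomisation by sex.

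Section {20c} defines the analysis set so that "every participant who took part in the baseline assessment is included in the final analysis". The S-NAB and the CFQ-D are both baseline measures, so the components of a baseline discrepancy should exist for everyone analysed. The article implies this baseline discrepancy but does not say outright that it will be calculated for each participant.

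**The concern.** The plan names an unadjusted two-sample test for a between-arm comparison when a baseline version of the same variable is to hand and its own main model would use it. None of the three readings of the sentence makes the t-test the better choice:

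- **Baseline discrepancy.** The arms are randomised and not yet treated, so the comparison carries no information about the app.
- **Follow-up discrepancy.** The test leaves out the baseline discrepancy and the sex stratum.
- **Change in discrepancy.** The test uses the baseline but fixes its coefficient at 1 instead of estimating it.

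At stake is the width of the confidence interval for the effect on self-estimation accuracy. A lesser matter is that the open time point leaves a choice among tests that could be made after the data are seen.

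**Working it through.** **Inputs from the article.** Sample size {14} plans for 164 analysed in the intervention group and 82 in the control group, with a standardised effect of 0.39, 80% power and a two-sided α of 0.05. The discrepancy analysis has no sample size or power figure of its own, so 164 and 82 are borrowed as the numbers with follow-up. Imputed follow-up values for drop-outs would add little information.

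**Input not in the article.** r, the baseline-to-follow-up correlation of the discrepancy. It is an assumption throughout and is shown as a range.

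**Reproducing the plan's figure.** A non-central t calculation with the Wilcoxon-Mann-Whitney efficiency of 3/π (normal data), effect size 0.39, two-sided 0.05 and 2:1 allocation gives power 0.801 at 164 + 82 = 246. The stated total is reproduced.

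**Formulas**, in units of the discrepancy's SD, assuming equal variance at both visits and a common slope in the two arms:

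- Follow-up t-test: SE = √(1/164 + 1/82) = √0.01829 = 0.1353.
- Change-score t-test: SE = 0.1353 × √(2(1 − r)).
- ANCOVA: SE = 0.1353 × √(1 − r²).
- Variance removed by ANCOVA against the follow-up test: 1 − (1 − r²) = r².
- Variance removed by ANCOVA against the change test: 1 − (1 − r²)/(2(1 − r)) = (1 − r)/2.
- Difference detectable with 80% power: (1.960 + 0.842) × SE.

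**Results**

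| r | SE follow-up t | SE change t | SE ANCOVA | Removed vs follow-up | Removed vs change | Detectable: follow-up / change / ANCOVA |
|---|---|---|---|---|---|---|
| 0.3 | 0.1353 | 0.1600 | 0.1290 | 9% | 35% | 0.379 / 0.448 / 0.361 |
| 0.5 | 0.1353 | 0.1353 | 0.1171 | 25% | 25% | 0.379 / 0.379 / 0.328 |
| 0.75 | 0.1353 | 0.0956 | 0.0895 | 56% | 12.5% | 0.379 / 0.268 / 0.251 |
| 0.8 | 0.1353 | 0.0855 | 0.0812 | 64% | 10% | 0.379 / 0.240 / 0.227 |

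A simulation of 4,000 trials at 164/82 gave reductions against the follow-up test of 25% (r = 0.5) and 57% (r = 0.75). Against the change test it gave 24% and 11%. These agree with the formulas to within simulation error and the small cost of estimating the slope.

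**How r depends on the definition of the score.** For a signed difference of two standardised scales with common retest correlation ρ, and correlation c between the scales within and across visits, r = (ρ − c)/(1 − c).

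- ρ = 0.6 to 0.8 with c = 0.2: r = 0.4/0.8 = 0.50 to 0.6/0.8 = 0.75, so r² = 25% to 56%.
- The same ρ with c = −0.2: r = 0.8/1.2 = 0.67 to 1.0/1.2 = 0.83, so r² = 44% to 69%. The sign of c matters because a high S-NAB score is good and a high CFQ-D score is bad, so it changes with whether one scale is reversed.
- Absolute discrepancy, centred bivariate normal: signed correlations of 0.50, 0.625 and 0.75 become 0.22, 0.35 and 0.52, so r² falls to about 5%, 13% and 27%.

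**The case against.** The strongest reply is that nothing is invalid here. In a randomised trial the unadjusted t-test is unbiased and keeps its type I error. A chance baseline difference does pass in part into a follow-up comparison, but the t-test's standard error already allows for it. The analysis is supplementary, self-estimation accuracy is not among the research questions in Objectives {7}, and no power target is set for it. The time point and score definition are details that a condensed article may leave to an analysis plan that is not shown. All of this stands, and it limits the point to precision. It does not dispose of it, because the test is named in the article and is less efficient than the model the same article uses for training effects.

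A reader might go further in several ways that the document does not support:

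- **That a quarter to a half of the variance is thrown away as a matter of fact.** No retest or cross-scale correlation is given. That range needs r between 0.50 and 0.75, a signed score and a follow-up-only test.
- **That the loss does not depend on how the discrepancy is signed or scaled.** The preference for ANCOVA does not, but the size of the gain does.
- **That this is the only unadjusted between-arm comparison in the plan.** Section {20a} also gives a Mann-Whitney fallback for training effects, with no baseline adjustment stated.
- **That the plan commits to a significance test at baseline, or ignores the baseline altogether.** The sentence fixes neither; a change-score test is a natural reading and would use the baseline.

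**Conclusion.** The point holds as one of efficiency. Section {20b} names a t-test at an unstated time point where the {20a} ANCOVA could be used on data already collected. The gain is r² over a follow-up-only t-test (9%, 25% and 56% at r = 0.3, 0.5 and 0.75) or (1 − r)/2 over a change-score t-test (25% and 12.5% at r = 0.5 and 0.75). With 164 and 82 analysed, the detectable difference falls from 0.38 SD to 0.33 SD at r = 0.5 and to 0.25 SD at r = 0.75 against the follow-up test. At r = 0.75 it falls only from 0.27 to 0.25 SD against the change test. All of this rests on an assumed r, equal variances at the two visits and a common slope; an absolute discrepancy would lower r and with it the gain over a follow-up-only test. A reader might infer bias, an inflated error rate or a threat to the main conclusion; none follows, and the primary analysis is untouched.

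**What to change.** In {20b}, replace the t-test sentence with one that:

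- names the follow-up discrepancy as the outcome and states whether it is signed or absolute;
- analyses it with the {20a} ANCOVA, with arm as factor and baseline discrepancy and sex as covariates;
- reports the adjusted mean difference with its confidence interval;
- reports the baseline discrepancy by arm descriptively, without a test.

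The correlational analysis can stay as a descriptive addition. The cost is one sentence of text and one degree of freedom per covariate, with no new data, visits or participants.
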